### Sample size

A sample size for analysis of 434 patients (217 per arm) who have complete data on systolic BP at 12 months will give 90% power to detect a 5 mmHg difference in mean systolic BP between arms, assuming a standard deviation of 16 mmHg (a conservative estimate based on the feasibility trial
^
22
^) and using a two-sided t-test at the 5% significance level. A 5 mmHg difference in systolic BP is of clinical significance, being associated with a 20% reduction in major vascular events.
^
62–
64
^ Assuming that 20% of participants do not provide systolic BP data at 12 months, 542 patients (271 per arm) will need to be randomised.

### Statistical analysis

In the analyses, an intention to treat (ITT) approach will be used, maintaining participants in the arm to which they were randomised.

For the primary outcome analysis, a linear mixed effects model will be used to compare the mean systolic BP at 12 months between the two arms and quantify this as a difference in means and 95% confidence interval. A p-value for this powered outcome will be reported and assessed against the two-sided 5% significance level. The outcome for this analysis will be 12-month systolic BP self-measured by monitor at home. But if there are missing data on this measure, an additional source of BP measures will be used, namely systolic BP measures from practice records closest to 12 months post-randomisation.

In a supportive model, there will be baseline covariate adjustment for sex, age, geographical region, the closest measure prior to randomisation of systolic BP obtained from practice records, and for the randomisation stratifier of practitioner as a random effect. Missing data in covariates will be handled using the missing indicator method.
^
65
^

A sensitivity analysis will be undertaken to examine the robustness of the main model analysis result to the ‘missing at random’ (MAR) assumption.
^
66
^ The aim is to adequately explore the impact of departures from the MAR assumption on the primary outcome results. This will be handled first within a ‘not-missing-at-random’ sensitivity analysis considering optimistic and pessimistic scenarios for the intervention effect size by arm in those with missing data, with results displayed graphically, as in a previously analysed trial.
^
67
^ Second, the impact will be explored by incorporating baseline predictors of primary outcome missing status that are differential by arm.

We will also conduct a Complier Average Causal Effect (CACE) analysis by defining a ‘compliant’ per protocol population analysis in those participants who did not stop the digital intervention in the first three months and corresponding ‘would-be compliers’ in the control arm.
^
68,
69
^

Secondary outcomes (including the other clinical outcomes and measures of medication adherence), being continuous, will be analysed using mixed models and interpreted from 95% confidence intervals.

Pre-specified subgroup variables will be examined in relation to the primary outcome and will involve an initial, indicative, test of differential intervention effect across the subgroup variable before summarising the intervention effect in each of two subgroup categories. The proposed subgroup variables comprise: sex; age group; geographical region; and deprivation (high versus low, based on the Index of Multiple Deprivation, derived from the patient’s home postcode
^
27
^). Assuming a sample size for analysis of 434 and equal sized categories, the intervention effect observed in each subgroup will be estimated with a 95% confidence interval having an informative width of +/- 4.3 mmHg.

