### Randomisation and blinding

During the baseline consultation, the practitioner will use an online system to check eligibility, obtain informed consent, obtain baseline questionnaire data, randomly allocate patients to the intervention or the control group, and, if the participant has been allocated to the intervention group, to deliver the very brief intervention (VBI). Eligible patients will be allocated randomly in a 1:1 ratio to receive the VBI followed by the digital intervention plus usual care or usual care only. The method of permuted blocks will be used with randomly varied block sizes of 4 and 6 and stratification by practitioner. Although the allocation sequence will be concealed, once a participant is allocated neither the practitioner nor the participant will be blind to group allocation. However, for some of the data collection and analysis procedures, it will be possible to maintain blinding. For example, staff at the laboratory who analyse the urine samples will not be aware of participants’ group allocation. Similarly, BP measures submitted by participants to the research team will be coded by staff who are not aware of the participants’ group allocation.

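### The primary analysis has no stated adjustment for pre-randomisation systolic BP and does not name its random effect, so it gives up precision that the plan already has the data to gain

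*Protocol article*

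**What the plan says.** The protocol article, under Statistical analysis, says that for the primary outcome "a linear mixed effects model will be used to compare the mean systolic BP at 12 months between the two arms". The difference in means, its 95% confidence interval and the one p-value judged at two-sided 5% all come from this model. No covariate and no random effect is named for it.

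The section then describes a second model: "In a supportive model, there will be baseline covariate adjustment for sex, age, geographical region, the closest measure prior to randomisation of systolic BP". The baseline value comes from practice records. The same sentence adds practitioner as a random effect, and missing covariate values are handled by a missing indicator.

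The section on Randomisation and blinding makes practitioner a design variable: "The method of permuted blocks will be used with randomly varied block sizes of 4 and 6 and stratification by practitioner".

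The Measures section says that up to two practice BP readings from the 12 months before randomisation are extracted. The home BP monitor is posted only after the baseline consultation, in which randomisation and the very brief intervention take place. The practice reading is therefore the pre-randomisation BP value available as a covariate.

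**The concern.** Earlier systolic BP is an obvious candidate predictor of later systolic BP, and the plan already extracts it and uses it, but only in the model that does not carry the p-value. Any non-zero correlation with the 12-month outcome means that the headline interval is wider than it need be. It also means that a chance difference between arms in starting BP stays in the headline estimate.

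The second matter is one of specification. Each participant has one 12-month outcome, so a mixed model needs some grouping factor. The only one the article names is practitioner, and it names it only for the supportive model. A reader cannot tell whether the primary analysis includes the stratifier or amounts to a plain two-arm comparison.

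At stake are the width of the headline interval and some power above the planned 90%. There is also the awkward case in which the two pre-specified models fall on either side of 5% and the less precise one is decisive.

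**Working it through.** **Inputs from the Sample size section.** Analysed sample: "A sample size for analysis of 434 patients (217 per arm) who have complete data on systolic BP at 12 months". Target: a 5 mmHg difference at 90% power. Variability: "assuming a standard deviation of 16 mmHg". Test: "using a two-sided t-test at the 5% significance level".

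**Inputs not in the document, so assumed.** The correlation r between the pre-randomisation practice reading and 12-month systolic BP (0.2 to 0.5), and the intraclass correlation (ICC) for practitioner (0.02 to 0.10).

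**Step 1: reproduce the plan's figures.**
- Standard error of the difference: 16 × √(2/217) = 1.536 mmHg.
- Power from the noncentral t distribution, with noncentrality 5/1.536 = 3.26 and 432 degrees of freedom: 90.1%. With 216 per arm it is 89.98%, so 217 is the smallest number that reaches 90%.
- Inflation for 20% missing: 434/0.8 = 542.5, stated as 542.
- Subgroup half-width, with 434/4 = 108.5 per arm in each category: 1.96 × 16 × √(2/108.5) = 4.26, stated as 4.3 mmHg.

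The sample size and the subgroup width both use the full SD of 16, which fits an unadjusted primary comparison.

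**Step 2: add baseline systolic BP.** Residual SD = 16 × √(1 − r²). Half-width = 1.96 × residual SD × √(2/217). Equivalent unadjusted sample = 434/(1 − r²).

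| Assumed r | Residual SD (mmHg) | 95% half-width (mmHg) | Power | Equivalent sample |
|---|---|---|---|---|
| 0 (unadjusted) | 16.00 | 3.01 | 90.1% | 434 |
| 0.2 | 15.68 | 2.95 | 91.2% | 452 |
| 0.3 | 15.26 | 2.87 | 92.6% | 477 |
| 0.4 | 14.66 | 2.76 | 94.3% | 517 |
| 0.5 | 13.86 | 2.61 | 96.3% | 579 |

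The interval narrows by 2.0%, 4.6%, 8.3% and 13.4% in turn.

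**Step 3: chance imbalance.** The part of the estimate's standard error due to baseline BP is r × 16 × √(2/217): 0.46 mmHg at r = 0.3 and 0.77 mmHg at r = 0.5, against a target of 5 mmHg.

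**Step 4: practitioner, if it is absent from the primary model.** Stratified 1:1 allocation nearly balances the arms within practitioner, so the true SD for the comparison is about 16 × √(1 − ICC), while an analysis that ignores practitioner still uses 16. The actual two-sided error rate is then 2 × [1 − Φ(1.96/√(1 − ICC))].

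| Assumed ICC | Half-width with practitioner (mmHg) | Power with practitioner | Actual error rate without it |
|---|---|---|---|
| 0.02 | 2.98 | 90.7% | 4.8% |
| 0.05 | 2.93 | 91.5% | 4.4% |
| 0.10 | 2.86 | 92.8% | 3.9% |

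With practitioner in the model the interval is about 1% to 5% narrower. Without it the test is slightly conservative.

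**The case against.** The plan is valid as it stands. An unadjusted randomised comparison is unbiased, its interval and p-value already allow for chance imbalance, and the trial was sized for it. The adjusted model is also pre-specified and will be reported. All of this stands. It makes the point one of efficiency.

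The gain may be small. The covariate is a practice reading up to 12 months old, the main outcome is measured at home, many participants are selected on raised BP, and some readings may be missing. At r = 0.2 the half-width falls by only 0.06 mmHg. This also stands, with two qualifications: patients can enter on prescription gaps alone, so the restriction of range is partial, and where home BP is missing the outcome is itself a practice reading.

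A reader might infer that the stratifier is definitely left out of the primary analysis. The article does not support that. It calls the primary model mixed, and practitioner is the only random effect named, so it may have been meant there too. Omission is the likelier literal reading, not a stated fact.

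A reader might also infer that missing data are handled on the strength of arm alone. The same section uses practice readings where home BP is missing, and plans missing-not-at-random scenarios by arm and a further analysis with baseline predictors of missingness. Those plans cover much of that worry.

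Finally, changing the primary model late is not free of risk. The article gives recruitment as January 2021 to March 2022, so 12-month follow-up fell due by about March 2023. This objection stands and shapes the fix.

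**Conclusion.** The point holds as a low-cost gain in precision and a gap in specification. The model that carries the p-value has no stated adjustment for pre-randomisation systolic BP, and its random effect is not named.

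The unadjusted half-width is 3.01 mmHg. Adjustment would bring it to between 2.95 and 2.61 mmHg, and power from 90.1% to between 91.2% and 96.3%, for assumed correlations of 0.2 to 0.5. The article gives no correlation, so the size of the gain cannot be fixed, and the lower end is plausible. The figures also assume a complete covariate with a linear relation to the outcome. Leaving practitioner out, if that is what is meant, costs about 1% to 5% in interval width at assumed ICCs of 0.02 to 0.10 and does not inflate false positives.

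It would be wrong to conclude that the trial is underpowered, that its estimate is biased, or that the sample size is in error. The plan's own figures reproduce without any gain from covariates.

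**What to change.** If no unblinded analysis has been done, make the adjusted model that is already specified the primary one: pre-randomisation practice systolic BP, age, sex and region as fixed effects, with a random intercept for practitioner. Take the p-value from it and report the unadjusted comparison as supportive. Date the change and record that it was made blind to outcomes by arm.

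If unblinding has already happened, keep the pre-specified primary model, so that the choice cannot be driven by the results. State which random effect it contains, and report the adjusted estimate and interval alongside it.

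The sample size needs no change. The covariates are already being collected and a rule for missing values is in place, so the cost is a change of wording in the protocol and analysis plan, with a documented check on when it was made.

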### Economic analysis

Overview

We will undertake a detailed analysis of the cost and cost-effectiveness of the PAM intervention compared with usual care alone using accepted economic evaluation methods.
^
70
^ We will estimate cost and cost-effectiveness for the within-trial period (12 months) and also over the expected lifetime of the patient. Costs will be assessed from the perspective of the NHS and personal social services (PSS). Cost components included in the analysis will consist of the detailed cost of the VBI and digital interventions, antihypertensive and other medications, use of NHS and social services, and costs incurred by patients. Unit costs will be taken from standard published sources.

Within-trial analysis

The cost-effectiveness measures in the within-trial analysis will be the incremental cost per change in systolic BP and the incremental cost per quality-adjusted life year (QALY) gained. Costs will be measured as described. During the within-trial period, resource use will be collected via retrospective questionnaire at six and 12 months covering the preceding six-month period. QALYs will be calculated based on the health related quality of life (HRQL) and mortality data collected during the trial. HRQL will be measured using the EQ-5D-5L
^
71
^ (
euroqol.org), collected at post-baseline, six months and 12 months for each patient. Utility scores will be calculated from the EQ-5D-5L descriptive system profiles using the recommended algorithm for the UK population at the time of analysis.

QALYs will be calculated for individual participants using an area-under-the curve approach, with linear interpolation between time points (post-baseline, 6 months, 12 months). Missing values of EQ-5D-5L and resource use will be imputed using multiple imputation incorporating variance correction factors.

The incremental cost-effectiveness ratio (ICER) will be calculated as the mean incremental cost divided by the mean QALYs gained for the intervention arm compared with usual care. Bootstrapped estimates of the mean differences in cost and QALYs will be used.
^
72
^ The incremental net monetary benefit (INMB) will be calculated as the difference in mean QALYs between the intervention and usual care arms, multiplied by the threshold value, minus the corresponding difference in mean costs. A cost-effectiveness acceptability curve (CEAC) will be constructed to show the probability that the PAM intervention is cost-effective at 12 months compared with usual care across a range of willingness-to-pay (WTP) thresholds. Probabilistic sensitivity analysis will be used to assess the impact of key assumptions on cost-effectiveness.

Long-run analysis

In the long-run analysis, cost-effectiveness will be calculated in terms of the incremental cost per QALY gained for the PAM intervention versus usual care. The analysis will incorporate and then extrapolate from the 12-month time period of the within-trial analysis. We will use a Markov model to estimate the long-term cost-effectiveness of the PAM intervention which will be based on a previous model from the TASMINH2 study.
^
73
^ This will account for age-related risks of CVD events over the life course as a function of systolic BP levels, which will in turn be influenced by adherence to antihypertensive medications. Costs and utility scores obtained from published studies will be assigned to health states. The analysis will assume varying durations of effect of the PAM intervention beyond those observed at 12 months on medication adherence and therefore systolic BP. We will undertake deterministic (one-, two- and multi-way) and probabilistic sensitivity analysis (including constructing a cost-effectiveness acceptability curve) assuming appropriate distributions and parameter values.
^
74
^

### Trial dates

Participants were recruited between January 2021 and March 2022.

## Ethics and dissemination

The study was approved by the East of England Cambridge East Independent Research Ethics Committee (REC reference
19/EE/0354, 05/02/2020), the Health Research Authority (HRA) and Health and Care Research Wales (HCRW).

The findings will be disseminated to the scientific community, participating practitioners and the public using a range of methods, including journal articles, conference presentations and the programme website. Primary care practices will disseminate aggregate results to the trial participants.

## Data Availability

No underlying data are associated with this article. Open Science Framework: SPIRIT Checklist 20.10.25.
https://doi.org/10.17605/OSF.IO/AJBNX
^
75
^ This project contains the following underlying data:
•SPIRIT Checklist•Patient information sheet•Patient consent form SPIRIT Checklist Patient information sheet Patient consent form Data are available under the terms of the
Creative Commons Attribution 4.0 International license (CC-BY 4.0).
